**Fig. 1 Fig1:**
[figure not shown]
Study process. *IG1* intervention group 1, *IG2* intervention group 2, *WCG* waiting control group

The study design will also be tested as part of the piloting process. This will involve reviewing the central components of the study, e.g., randomization, recruitment procedures, inclusion and exclusion criteria, comparability of samples, and participation rates. Likewise, the intervention effect and the intra-cluster correlation coefficient (ICC) will be estimated in order to provide a suitable basis for calculating the sample sizes for a future confirmatory study.

The feasibility of the intervention will be evaluated using qualitative methods. In the course of the post-measurements, problem-focused individual interviews (half standardized) will be conducted with a random selection of participants (for approximately 10% of the participants) from IG1 (*N* = 18) and IG2 (*N* = 18).

### Study setting and recruitment

Hospitals geographically located in areas around the three study sites (Hamburg (North-West Germany), Bonn (Middle-West Germany) and Freiburg (South-West Germany)) can participate in the study. A list of study sites can be obtained from consortium leaders in Freiburg. Hospital recruitment will be organized non-randomly by each of the three study sites according to pre-defined criteria for participating wards: (1) inpatient care teams with a minimum of 10 members, (2) inpatient care teams with an inter-professional composition. Pediatric, emergency and intensive care wards will be excluded from participating in the study, as teamwork is highly regimented in pediatrics and emergency care, and patient involvement would not be comparable to other wards. Moreover, inpatient care teams with less than 10 members and mono-professional teams will be excluded. Participating hospitals will be asked to assign a local study coordinator, who supports the research team in local staff recruitment, organization of the intervention, and data collection at the wards. The following inclusion criteria for the participants are mandatory: (1) being a member of the participating inter-professional inpatient care team (e.g., physicians, nurses, physiotherapists, speech therapists, ergo therapists), (2) being at least 18 years old and (3) being fluent in German. Team members of mono-professional teams, team members under the age of 18 years and team members who are not able to speak German fluently will be excluded from participating in the study.

### Sample size

As the anticipated effect of the intervention on the primary and secondary outcomes is unclear, one of the aims of the feasibility study is to estimate this effect, in preparation for a confirmatory study [40]. Thus, the required sample size is determined on the basis of the identification of important rare (predicted or unpredicted) events [42]. In order to identify an event which occurs in 10% of cases with a confidence interval of 95%, 30 people have to be investigated in each relevant subgroup [42]. A conservative minimum of 10 employees per inpatient care team on the wards (cluster) will be taken as a starting point, so the three study sites each comprise nine wards (three per study arm). This means that viable data from a total of 90 participants (30 in IG1, IG2 and WCG, respectively) must be collected at each study site. As we anticipate a dropout rate of up to 25%, 12 wards will be recruited at each study site and randomly assigned to the three study arms. Thus, the study will in total include 36 wards with a minimum of 360 participants across three sites (10 participants * 4 wards * 3 study arms * 3 study sites).

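### The 95% chance of seeing a 10% event among 30 people per site and arm ignores ward clustering, and the 360 participants are a target, not a minimum

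*Protocol article*

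**What the plan says.** The Sample size section of the protocol article sets effect-based sizing aside, because the effect is unknown, and sizes the study on detecting rare events instead: "In order to identify an event which occurs in 10% of cases with a confidence interval of 95%, 30 people have to be investigated" per subgroup. It then builds the 30 from wards: "A conservative minimum of 10 employees per inpatient care team on the wards (cluster) will be taken as a starting point", and "the three study sites each comprise nine wards (three per study arm"). The requirement is set within site and arm: "viable data from a total of 90 participants (30 in IG1, IG2 and WCG, respectively) must be collected at each study site". To allow for up to 25% dropout, nine wards per site become 12, and the section concludes: "Thus, the study will in total include 36 wards with a minimum of 360 participants across three sites".

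The 10 per ward matches a ward eligibility criterion in Study setting and recruitment: "inpatient care teams with a minimum of 10 members". The same section excludes individual members who are under 18 or not fluent in German.

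Elsewhere the article treats wards as correlated clusters. In Study design they are the units of randomization and an ICC is to be estimated. In Data analysis the model has a random intercept for ward.

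**The concern.** The detection property is the only quantitative justification for the sample size, and it is stated for each arm at each site. It is calculated as if the 30 people were independent, yet they work in a handful of wards and the rest of the article expects people in one ward to resemble each other. Where events cluster by ward, 30 people in three or four wards are less likely to show at least one event than 30 unrelated people. The in-person training is given to actual teams, so some implementation problems could well be shared within a ward.

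Calling the figure a confidence interval is loose wording. What is meant is a 95% probability of seeing the event at least once.

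The total has a related weakness. Team members and participants are treated as the same number, so a figure called a minimum is reached in 10-person teams only if every member is eligible and takes part. The pilot is meant to inform the sizing of a confirmatory trial, so its own sizing statement should be correct as written.

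**Working it through.** **Inputs from the Sample size section:** event prevalence p = 0.10; 30 people per arm and site; 10 per ward; three wards per arm and site before the dropout allowance and four after it; dropout up to 25%; total 36 wards and 360 people. **Not given:** the ICC (assumed here between 0.01 and 0.20) and the participation rate.

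**1. The plan's own figures.** For independent people, P(at least one event) = 1 − (1 − p)^n.
- n = 28: 94.8%
- n = 29: 95.3%
- n = 30: 1 − 0.9^30 = 95.8%

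So 30 reproduces, with less than one percentage point to spare. The totals reproduce too: 9/0.75 = 12 wards per site, 270/0.75 = 360, and 10 × 4 × 3 × 3 = 360.

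**2. With clustering.** Let the event rate vary between wards as a beta distribution with ICC r: a = p(1 − r)/r and b = (1 − p)(1 − r)/r. The probability of no event in a ward of m people is P0(m) = the product over j = 0, …, m − 1 of (b + j)/(a + b + j). For k wards of m people, P(at least one event) = 1 − P0(m)^k.

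Example with r = 0.05: a = 1.9, b = 17.1, P0(10) = 0.424, and 1 − 0.424^3 = 92.4%.

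The 30 people may sit in three wards of 10 (if dropout removes whole wards) or in four wards of 7 or 8 (if it removes individuals):

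| ICC (assumed) | 3 wards of 10 | 4 wards of 7 or 8 | 9 wards of 10, pooled per arm |
|---|---|---|---|
| 0 | 95.8% | 95.8% | >99.9% |
| 0.01 | 95.1% | 95.3% | >99.9% |
| 0.02 | 94.4% | 94.8% | >99.9% |
| 0.05 | 92.4% | 93.3% | >99.9% |
| 0.10 | 88.7% | 90.6% | 99.9% |
| 0.20 | 81.2% | 84.9% | 99.3% |

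The probability crosses 95% at an ICC of about 0.012 with three wards and about 0.016 with four.

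**3. The total of 360.** Applying the dropout allowance gives 360 × 0.75 = 270 = 3 × 90, exactly the number of people from whom viable data are required. Nothing is left for members who are ineligible or decline. For illustration only, assume every ward has exactly 10 members and 80% take part. Then 360 × 0.80 = 288 enrol, and 40 × 0.80 × 0.75 = 24 remain per arm and site. Even if independent, these give 1 − 0.9^24 = 92.0%.

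**The case against.** Much of the opposing case is sound.

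- **There is no arithmetic error.** Every figure in the section reproduces under its assumptions. A reader might infer a miscalculation, but the fault is an independence assumption that is not stated and does not fit the design.
- **Participation is not a condition of the 95%.** The 30 are people with viable data, so uptake affects only whether 30 is reached, not the probability once it is.
- **The size of the loss is unknown.** The ICC is one of the quantities the pilot will estimate. At 0.01 the loss is trivial and at 0.02 it is about one point. A claim that detection is clearly below 95% would go beyond the documents.
- **Four wards per arm and site are recruited, not three.** The Discussion links dropout to the three assessments, which suggests loss of individuals. That favours the four-ward column, which is higher but still below 95% from an ICC of about 0.016.
- **Ten is a floor for team size.** Larger teams could offset non-participation. The interview plan in Study design (18 people as about 10% of each intervention group) implies roughly 18/0.10 = 180 per arm, against 120 here. The article does not reconcile the two.
- **The consequence is limited.** Pooled per arm, detection exceeds 99% across the whole range.

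What the objection does not remove is that the section itself sets the requirement per arm at each site. At that level the stated 95% has almost no margin, and any clustering worth modelling takes it below.

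**Conclusion.** The point holds in a limited form. The 95% probability of seeing a 10% event among 30 people is correct for independent people (95.8%). It is not delivered per site and arm unless the ICC is about 0.01 or less. Over an assumed ICC of 0.01 to 0.20 it is about 95% to 81% with three wards of 10, and 95% to 85% with four wards of 7 or 8. These values rest on a beta-binomial model with equal or near-equal ward sizes and on an ICC range that the documents do not supply.

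The 360 is likewise not a guaranteed minimum. It requires an average of 10 eligible, participating members per ward, and the 25% allowance is fully used by dropout. Whether recruitment will fall short cannot be told from the documents.

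A reader might conclude that the trial is too small or needs more wards. The documents do not support that: detection pooled per arm stays above 99%, and the planned analysis already allows for ward effects.

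**What to change.** Reword two statements in the Sample size section.

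1. Replace the sentence on the 10% event with, for example: *The probability of observing at least once an event of 10% prevalence among 30 participants per site and arm is 95.8% if they are independent. Over an assumed ICC range of 0.01 to 0.20 it is about 95% to 81% if they come from three wards of 10, and 95% to 85% if they come from four wards of 7 or 8. Pooled per arm (90 participants in nine wards) it exceeds 99%.* This also removes the reference to a confidence interval.

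2. Replace the minimum with: *a target of 360 participants (36 wards with at least 10 team members each)*. Add that reaching it needs an average of 10 eligible, participating members per ward, because the 25% allowance covers dropout only. Describing the 360 as eligible staff would not do, since some team members are excluded individually.

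The cost is a rewording and a slightly less favourable stated figure. No wards need to be added and no analysis changes.

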### Intervention

The intervention is didactically based on adult learning theories [43] and consists of a combination of e-learning and inter-professional, behavior-based team training performed in-person (blended learning) and involving a high level of interaction among team members. With regard to the content, basic competencies for patient safety will be imparted in the three key areas *Teamwork*, *Error management,* and *Patient involvement*.

In the following, the intervention is described according to the Templates for Intervention Description and Replication (TIDieR) [44].

Participants can access the online e-learning platform via a link. The e-learning course can be completed individually independent of time and location and allows for self-directed learning [45]. First, a video is presented, which introduces the topic of patient safety and demonstrates how to handle the e-learning course. For each key area a 1-h module is provided. The three modules are divided into submodules, which last from 5 to 10 min. The participants can go through as many single submodules, as they have time in a row. They have the opportunity to interrupt the process and restart from the same point at a later time. Within each module, an introduction video, presenting an overview of the content of the module, is provided. A variety of learning materials are used (instructional videos, interactions within text-based and audio-visual content). A section with take-home information concludes each module. Figure 2 provides an overview over the submodules. As an incentive, physicians get Continuing Medical Education (CME) credits and registered nurses get continuing education credits.

**Fig. 2 Fig2:**
[figure not shown]
Overview over the submodules

The participants have a maximum of 6 weeks to complete the whole e-learning course. They will be reminded twice (after 2 weeks and after 4 weeks). Moreover, a poster in their ward rooms reminds them to participate. In addition, they will receive cups and pens with the study logo as encouragement to participate.

The in-person training will take place in the actual teams in which the participants work. It will be conducted 1 to 4 weeks after the participants have completed the e-learning course. Behavior-related, practical exercises corresponding to the three key areas will be performed to facilitate the transfer of the theoretical content from e-learning into routine practice. Within the key area *Teamwork*, a video analysis will be conducted. Therefore, participants have to find mistakes in inter-professional teamwork seen in the video (corresponding to the e-learning submodules) and make appropriate recommendations for improving the inter-professional teamwork. Within the key area *Error management*, they have to do a detailed case analysis of a provided CIRS (Critical Incident Reporting System) case with the help of an Ishikawa chart [46]. Within the key area *Patient involvement*, the participants have to act out a role play on the subject “Communicate an adverse event.” Participants’ experiences and challenges regarding communication and behavior will be discussed after the role play. At the end, an action plan including important take-home information for each key area will be established.

The in-person training is expected to last for 210 min including breaks, which is considered realistic and resource-friendly. It will be conducted by psychologists, educationalists, nurses and public health scientists of our research team with experience in group moderation and adult education courses. These moderators will be trained in a train-the-trainer workshop by the consortium leaders. A trainer manual will provide the basis for the training and will contain information on the framework conditions (location, premises, duration and participants), the training schedule, and the content of the three key areas (including objectives, methods, and materials).

The intervention promotes all components of the KSA framework (Knowledge, Skills, Abilities) [47] in the three key areas. The intervention will take place at an employee level (e-learning) and a team level (inter-professional in-person training), but will also address the organizational and patient level. The intervention will be carried out at cluster level. In accordance with a flipped classroom approach (the trainees will prepare for the in-person training through e-learning), the participants of IG2 (blended learning group) will start with the e-learning course, where they work individually on the theoretical foundations for the three key areas (knowledge). Subsequently, the participants of IG2 will try out (skills) and consolidate (abilities) their knowledge in the in-person training. IG1 participants will work exclusively on the e-learning course. The WCG will not initially be assigned to an intervention, but will be given the opportunity to participate once the follow-up measurement has been concluded (see Fig. 3). Figure 3 shows a schedule of study enrolment, interventions and assessments. The recommendations for interventional trials (SPIRIT) checklist [63] is available as Additional file 1.

**Fig. 3 Fig3:**
[figure not shown]
Schedule of enrolment, interventions and assessments (as per Standard Protocol Items: Recommendations for Interventional Trials (SPIRIT) Figure [63])

### Outcomes

The primary outcomes in the pilot study are *Safety-related behavior regarding Teamwork, Error management and Patient involvement* and S*ubjectively perceived patient safety.* The secondary outcomes are aspects of *Teamwork*, *Error management* and *Patient involvement*.

### Measuring the outcomes

As part of piloting the intervention, all outcomes will be measured at the individual level. Primary and secondary outcomes will be assessed at three points in time (pre, post and follow-up) by an online survey for the purpose of a summative evaluation. It will take approximately 20 min to complete this survey. There is also a paper version of the survey available. For the primary outcomes, situational judgement tests [48–50] will be used. They were pretested within an expert workshop with different members of inter-professional teams (e.g., physicians, nurses, therapists). The situational judgement tests describe typical everyday situations specifying five possible realistic behaviors. The participants have to rank the behaviors in the way that they most likely would react (ranging from (1) this approach is closest to my reaction, to (5) this approach is the least of my reactions). The ideal sequence, based on results of the expert workshop, will be scored with 30 points (4*4 + 3*3 + 2*2 + 1*1 + 0*0). The worst sequence will be scored with 10 points (4*0 + 3*1 + 2*2 + 1*3 + 0*4). The secondary outcomes will be assessed by validated scales and single items from standardized questionnaires. (e.g., *Teamwork* = Abridged version of the Questionnaire on Working in a Team (FAT-K) [51], Revised Nursing Work Index (NWI-R) [52], Scale to assess knowledge integration problems in interdisciplinary project teams (WIP) [53]; *Error management* = Error Orientation Questionnaire (EOQ) [54], Safety Attitudes Questionnaire (SAQ) [55], German short version of the Attitudes towards Patient Safety Questionnaire (G-APSQ short) [56] Safety Organizing Scale (SOS) [57], Psychological Safety Questionnaire [58]; *Patient involvement:* ThinkSAFE Patient Safety Questionnaire [59], Provider-Patient-Relationship Questionnaire (PPRQ) [60]. Items will be answered on 5-point Likert scales (ranging from totally disagree (1) to totally agree (5). A list of all included questionnaires is provided in Fig. 3.

Once the intervention components (e-learning, in-person training) have been completed, the feasibility of the intervention will be investigated for the purposes of a formative evaluation. To evaluate the e-learning, a short online survey will be conducted with all e-learning participants. To evaluate the in-person training, a paper-pencil survey will be conducted with all in-person training participants. Both surveys will last approximately 5 min. The intervention components will be evaluated with regard to satisfaction and acceptance. Additionally, the user-friendliness of the e-learning course will be measured. Therefore, validated scales from standardized questionnaires will be used [61, 62]. Furthermore, items will be designed which reflect the specific characteristics of e-learning (e.g., the option of interrupting the e-learning course and restarting from the same point).

To evaluate the feasibility of the intervention, problem-focused individual interviews will be conducted. Within these interviews, the acceptance, feasibility and user-friendliness of the intervention components will be examined from the perspective of the participants, and barriers to participation and promoting factors, which could have an impact on primary and secondary outcomes, will be explored.

Figure 3 provides the schedule of enrollment, interventions and assessments.

### Data collection and management

To access the online survey regarding summative evaluation, all participants will receive an email with a unique link to the online survey at each time of assessment (pre, post and follow-up) (see Fig. 1) from the local study coordinator. Lists with contact details of participants will be stored by the local study coordinator at participating hospitals. None of the researchers at the study sites will have access to any contact information of the participants. If required, participants can download a paper version of the survey and return questionnaires by mail to the study sites. Moreover, wards that do not provide email access for participants will receive a paper version of the survey coded with the ward number for unambiguous allocation of returned surveys. With the latter option, questionnaires will be collected in a survey mailbox at the wards or can be mailed directly to the study sites. For ensuring the allocation of individual paper-pencil and online data for pre, post and follow-up surveys, participants will be asked to create an individual four-digit ID to be entered in the survey. In order to raise response rates at each time of assessment, participants will receive at least two reminders via email 2 and 4 weeks after the initial invitation to the survey. In case of distributed paper-pencil questionnaires, the local study coordinator will send at least two postal reminders or give verbal reminders in team meetings at the wards. In addition, a poster in the ward rooms will remind them to participate.

Online surveys (pre, post and follow-up) will be entered by participants and pseudonyms stored on the survey projects at QuestBack server park (located in Bremen, Germany), a BSI-certified data center ensuring stringent security requirements. Paper-based questionnaires collected at the three study sites will be entered to the online survey platform (Unipark) by researchers, following data entry rules agreed in the study consortium. For quality assurance, 10% of the paper-based survey entries will be reviewed independently by a second researcher at the study sites. After the completion of the data collection, raw data will be downloaded in analyzable formats such as IBM SPSS Statistics 25.

Concerning the formative evaluation of the e-learning, a link in the e-learning course will lead the participants directly to the corresponding online survey. Data will be collected anonymously and will be entered by participants. They were also stored at QuestBack server park. Concerning formative evaluation of the in-person training, data were collected via paper-based survey right after the in-person training. These anonymous surveys will be gathered in a mailbox. The collected data will also be entered into an online survey platform (Unipark) by researchers following the same rules as is stated above.

The problem-focused interviews will be carried out with the help of a half standardized interview guide by members of our research team. The interviewer will be trained by the consortium leaders. The interviews will be conducted via phone and recorded on tape. Before the interview, participants will sign a declaration of consent for the electronic recording, transcription and use of data for publications and lectures. In addition, they will sign an information leaflet of data confidentiality in accordance with the European General Data Protection Regulation (EU-DSGVO). The tape material will be transcripted by researchers according to transcription rules of Dresing and Pehl [64]. For the transcription and the subsequent evaluation MAXQDA Plus 12 software (VERBI Software GmbH, VERBI Software Company) will be used. The data will be stored on password-protected computers. All personal data will be deleted during the transcription process. All participants will be given a pseudonym during the evaluation to guarantee data confidentiality and ensure that no conclusions could be drawn regarding the identity of the individuals.

Due to data security aspects, data from the KOMPAS study will not be made available in the public domain. By the end of the project, survey projects will be archived and deleted from QuestBack server. All data will be stored in accordance with national and regional data security standards.

